#### Sample size

Estimating the median DOTs in the Netherlands during the pre-implementation period is challenging due to the lack of data on the exact duration of antibiotic treatment for EOS in Dutch neonates. However, a mean antibiotic initiation rate of 3.8% of all live-born neonates was reported in 13 secondary Dutch hospitals.^40^ Additionally, another study among Dutch hospitals found that antibiotics were continued intravenously for more than 72 hours in 31.5% of cases in.^41^ Since neonates in the Netherlands are usually treated for either 24–72 hours (average 2 days) or 7 days, we can estimate the pre-implementation DOTs to be 136 per 1000 live-births (calculated as follows: (0.685×38 neonates×2 days) + (0.315×38 neonates×7 days)). This estimate matches the mean antibiotic exposure in other high-income countries, which is 135 (range 54–491) DOTs per 1000 live births as reported in the AENEAS study.^1^ Our goal for the post implementation period is to reduce the antibiotic initiation rate to 2% and halve the number of full treatment courses, aiming for 60 DOTs per 1000 live-births. However, we consider a reduction of at least 10% of DOTs to be clinically relevant. This would result in a post implementation outcome of 121.5 DOTs per 1000 live-births. Assuming a power of 90% and an alpha of 5%, a sample size of 2790 (1395 per group) would be required. This sample size will be feasible for both the total study population and most individual sites, since Dutch hospitals typically report annual birth rates ranging from 1000 to 3500, averaging approximately 2500 births per hospital per year. However, in hospitals with already low pre-implementation DOTs, no differences in absolute DOTS or trends may be found. This is acceptable, as this would demonstrate that these hospitals are already leading in the reduction of antibiotic use, and finding a difference through greater sample size would not be clinically relevant.

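### The 90% power claimed for 1,395 births per period is about 7% on the plan's own figures; a 10% fall in DOT needs about 74,000–77,500 births per period

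*Protocol article*

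**What the plan says.** The Sample size section builds a pre-implementation figure of 136 DOT per 1000 live births from three inputs: "a mean antibiotic initiation rate of 3.8% of all live-born neonates was reported in 13 secondary Dutch hospitals"; "antibiotics were continued intravenously for more than 72 hours in 31.5% of cases"; and courses of either about 2 days or 7 days. It compares this with a cited international study, "which is 135 (range 54–491) DOTs per 1000 live births".

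Its goal is 60 DOT per 1000, but it treats a 10% reduction, to 121.5, as the smallest relevant effect, and attaches the sample size to that: "Assuming a power of 90% and an alpha of 5%, a sample size of 2790 (1395 per group) would be required". No SD, formula or sidedness is given.

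The unit is live births, because feasibility is judged against births: "This sample size will be feasible for both the total study population and most individual sites, since Dutch hospitals typically report annual birth rates" of 1000 to 3500, on average about 2500. The section then says that hospitals with low pre-implementation DOT may show no difference and that "this would demonstrate that these hospitals are already leading in the reduction of antibiotic use".

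The Analysis section (Primary outcome) plans a mixed-effects segmented regression on at least four quarters before and four after, plus a before-after t-test or Mann-Whitney U test.

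**The concern.** About 96% of births contribute zero DOT and a few contribute 2 or 7, so the SD per birth is several times the mean. A 10% difference in such a mean cannot normally be detected with 1,395 births per group, which contain only about 53 treated neonates (1,395 × 0.038).

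At stake is how the results are read. If 90% power for a 10% fall is believed for the pooled study and for most single sites, a non-significant result will be taken as good evidence that no relevant fall occurred. At site level that inference would have almost no basis; in the pooled data it would be much weaker than stated.

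**Working it through.** **Inputs.** From Sample size: initiation 3.8%, long courses 31.5%, course lengths 2 and 7 days, means 135 (or 136) and 121.5 per 1000, alpha 5%, power 90%, births per hospital. From Study setting: 11 hospitals. Assumptions: two-sided test, independent births, untreated neonates count 0.

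**1. The plan's figure.** (1.960 + 1.282)² = 10.507. For two means, n per group = 2 × 10.507 × SD² / Δ². With Δ = 135 − 121.5 = 13.5 per 1000, n = 1,395 requires SD = 13.5 × √(1395/2) / 3.2415 = 110 per 1000, or 0.11 DOT per birth.

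**2. Is that SD possible?** DOT is a count of whole calendar days, so E[X²] is at least the mean. With mean 0.135, the variance is at least 0.135 × 0.865 = 0.1168 and the SD at least 0.34. Even at this floor (every treated neonate has exactly one day), n = 10.507 × (0.1168 + 0.1067) / 0.0135² ≈ 12,900 per period.

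**3. SD from the plan's own mix.**
- Mean: 0.038 × (0.685 × 2 + 0.315 × 7) = 0.13585, the plan's 136 per 1000.
- E[X²]: 0.038 × (0.685 × 4 + 0.315 × 49) = 0.69065.
- Variance: 0.69065 − 0.13585² = 0.6722; SD 0.820.
- Post-period variance if initiation falls by 10%: 0.6066.

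**4. Births needed per period for a 10% fall, 90% power.**
- Equal variances: 2 × 10.507 × 0.6722 / 0.0135² ≈ 77,500.
- Smaller post-period variance: 10.507 × (0.6722 + 0.6066) / 0.0135² ≈ 73,700.
- Starting from 136 (Δ = 14.5), or if only long courses fall: about 61,000–70,000.

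**5. Power with 1,395 per period.** SE = √((0.6722 + 0.6066)/1395) = 0.0303, or 30.3 per 1000. Power for 13.5 is 7.3%. Other variants give 6–8%. Simulated from the 0/2/7-day mix, the t-test has 7.3–7.9% and the Mann-Whitney test 4.9–8.4%.

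**6. Other readings of 1,395.** Poisson counts need 14,788 per group, and treating 0.135 and 0.1215 as proportions needs 12,890. A one-sided test with SD 0.82 needs about 63,200. If 1,395 meant treated neonates, it would take 1,395 / 0.038 ≈ 36,700 births per period, more than the 27,500 expected, so the feasibility sentence would fail.

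**7. What the expected births can detect (before-after contrast, no heterogeneity).** For the detectable fall, the post-period variance falls in step with initiation. The goal column uses 2% initiation and half the share of long courses (post-period variance 0.2186).

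| Births per period | Power, 10% fall (Δ 13.5 to 14.5) | Fall with 90% power, per 1000 | Power, 136 to 60 |
|---|---|---|---|
| 1,000 (small site) | about 7% | 96 (71%) | 72% |
| 2,500 (average site) | 9–10% | 66 (48%) | 98% |
| 3,500 (large site) | 11–12% | 57 (42%) | 99.7% |
| 27,500 (11 × 2,500) | 51–57% | 22 (16%) | above 99.9% |

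If all 11 sites had 1,000 or all had 3,500 births, pooled power for Δ = 13.5 would be 24% or 65%.

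**8. Interrupted time series.** Take 27,500 births per period in four quarters each, only between-birth variance, and the level change read at the first post-implementation quarter. With the listed terms (phase, time after the intervention) the SE is about 9–10 per 1000, giving about 29–31% power for 13.5. If a baseline trend is added and extrapolated over the 9-month gap, the SE is about 26 and power about 8%.

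**The case against.** **The plan aims much higher than 10%.** Its goal is 60 DOT per 1000, and for that goal an average site has about 98% power. This stands. A reader might infer that no single site is adequately sized for anything; the figures do not support that. But the article attaches its 90% to the 10% effect, and there the statement is wrong.

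**The SD is not in the document.** True, and an article may leave it out. The finding is not that it is missing. The stated inputs contradict the stated n, and the whole-day floor in step 2 does so without any assumption about course lengths.

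**Where 1,395 came from.** One quarter of the cited range, (491 − 54)/4 = 109.25 per 1000, gives 1,376, close to 1,395. A reader might infer that the spread of aggregate rates was used as the SD of a single birth. That is plausible, but the document does not say so, and the error does not depend on it.

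**Sizing on the before-after comparison is legitimate.** It is planned for the primary outcome alongside the time series, so this choice is not a fault in itself. A reader might also infer that the time series has only 8% power. That requires a baseline trend, which the Analysis section does not list among the fixed effects.

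**The remark on low-DOT hospitals is narrow.** It concerns hospitals already low before implementation and does not treat every null site result as success. This stands; only the reasoning from a null difference is weak.

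**Nothing in the conduct depends on n.** All births in fixed windows are used and 95% CIs are planned. This stands and limits the repair to the text.

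**Conclusion.** The stated power is wrong for the effect to which it is attached. On the plan's own figures, 1,395 births per period give about 7% power for a fall to 121.5 DOT per 1000, not 90%, and the births needed are understated about 50-fold (73,700–77,500 against 1,395).

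It would go too far to say that a 10% fall would usually be missed in the pooled data: at about 27,500 births per period the chance of detecting it is roughly even.

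These figures rest on the 0/2/7-day mix, a two-sided test, independent births and the assumed 2,500 births per hospital. More variable durations or hospital heterogeneity would raise the need. The more favourable readings lower it to about 61,000 and leave the conclusion unchanged.

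**What to change.** Text changes to the Sample size section; no extra births and no change to conduct:

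- Restate the calculation with the per-birth SD of 0.82, its derivation and the sidedness: about 74,000–77,500 births per period for 90% power at a 10% fall.
- State what the expected births can detect: about 22 DOT per 1000 (16%) with 90% power at 27,500 per period, before heterogeneity.
- Limit the single-site claim to large effects such as the goal of 60 DOT per 1000.
- Say that this sizing covers the before-after contrast, and give the precision of the time-series level change separately for the model actually fitted.
- Report site results as estimates with 95% CIs, and rest any statement that a hospital already leads on its baseline DOT, not on a non-significant change.

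The cost is that the stated sensitivity becomes less favourable: a 10% fall can no longer be presented as reliably detectable, pooled or by site.

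### The sample size of 1395 births per group implies a per-birth SD of 0.11 day, whereas the same paragraph's inputs give 0.82 day, so the claimed 90% power for a 10% reduction does not hold

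*Protocol article*

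**What the plan says.** The Sample size section builds the baseline from 3.8% of live births starting antibiotics, 68.5% of them treated for about 2 days and 31.5% for 7 days: "0.685×38 neonates×2 days) + (0.315×38 neonates×7 days". It notes agreement with an international mean, "which is 135 (range 54–491) DOTs per 1000 live births". It sets a goal of 60 DOT per 1000 but bases the sample size on a smaller effect: "we consider a reduction of at least 10% of DOTs to be clinically relevant", and "This would result in a post implementation outcome of 121.5 DOTs per 1000 live-births". The result is: "Assuming a power of 90% and an alpha of 5%, a sample size of 2790 (1395 per group) would be required". No SD, test or sidedness is stated.

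The unit is live births, because feasibility is judged against annual births per hospital (1000 to 3500, average about 2500): "This sample size will be feasible for both the total study population and most individual sites".

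The Analysis section, under Primary outcome, leads with a mixed-effects segmented regression and adds a before-after comparison by t-test or Mann-Whitney U test.

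**The concern.** The stated effect, power, alpha and group size together fix one SD. The stated treatment mix fixes another. They differ by a factor of about 7.5, so the required sample size differs by a factor of about 55.

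At stake is how results will be read. The article presents 90% power for its own smallest relevant effect as attainable overall and in most single hospitals. A reader who accepts this would take a non-significant result at one site as evidence against a relevant reduction, when a true 10% fall there would nearly always be missed.

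**Working it through.** **Inputs** (Sample size section unless noted): 3.8% of births treated; 68.5% for 2 days, 31.5% for 7 days; 135 versus 121.5 DOT per 1000, a difference of 0.0135 day per birth; 90% power; alpha 5%, taken as two-sided; 1000 to 3500 births per hospital per year, average 2500; 11 hospitals and 12-month periods (Study setting and population; Study design).

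**1. Reproducing 1395.** For two means, n per group = 2 × (1.960 + 1.2816)² × SD² / difference². Solving for the SD: 0.0135 × √(1395/2) / 3.2415 = 0.110 day. Putting 0.110 back gives n = 1395.2. With one-sided alpha the implied SD is 0.122. Other routes (Poisson rates, two proportions, starts only, treated neonates only, the goal scenario; one- and two-sided) do not come within 3% of 1395.

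**2. SD from the paragraph's own inputs.**
- Mean = 0.038 × (0.685 × 2 + 0.315 × 7) = 0.13585 day.
- Mean square = 0.038 × (0.685 × 4 + 0.315 × 49) = 0.6907.
- SD = √(0.6907 − 0.13585²) = 0.820 day.

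**3. Lower bounds.** If every treated neonate had the same 3.575 days, the SD would be 0.68. The Primary outcome section counts DOT in calendar days. A whole-number count with mean 0.135 has an SD of at least √(0.135 × 0.865) = 0.342. Even there, n = 2 × 3.2415² × 0.342² / 0.0135², about 13,500 per group, and power at 1395 is 18%.

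**4. Required size with SD 0.82.** n = 2 × 3.2415² × 0.820² / 0.0135², about 77,500 per group.

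**5. Power for a 10% reduction.** Power = Φ(r − 1.96) + Φ(−r − 1.96), with r = 0.0135 / (0.820 × √(2/n)).

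| Births per period | Power |
|---|---|
| 1395 | 7% |
| 2500 (average site) | 9% |
| 3500 (largest quoted site) | 11% |
| 11,000 (11 × 1000) | 23% |
| 27,500 (11 × 2500) | 49% |
| 38,500 (11 × 3500) | 63% |

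**6. Sensitivity at 27,500 births.** A smaller post-period SD gives 51–53%; a baseline of 135.85 with a difference of 14.35 gives 54%; SD 0.68 gives 64%. If the whole fall came from fewer starts (3.8% to 3.42%), a comparison of starts has r = 0.0038 / √[(0.038 × 0.962 + 0.0342 × 0.9658)/27,500] = 2.39, or 67% power.

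**7. Reduction detectable with 90% power.** 3.2415 × 0.820 × √(2/n) gives 22.7 per 1000 at 27,500 births (22.7/135 = 17%), 35.8 at 11,000, 19.2 at 38,500 and 75.2 at a single site of 2500.

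**8. The goal of 60 DOT per 1000** (difference 75). With SD 0.82 in both periods, n is about 2,510 per group. In the goal scenario (2% starts, share of full courses halved) the post-period SD is √[0.02 × (0.8425 × 4 + 0.1575 × 49) − 0.05575²] = 0.47. Then n = 3.2415² × (0.820² + 0.468²) / 0.075², about 1,660. At 2500 births, power for the goal is about 90% to 98%.

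**The case against.** The best defence is that 1395 governs nothing in practice. Data are extracted for all treated neonates over fixed 12-month periods, the main analysis is the time series model, and the goal is far larger than 10%. Much of this stands, and it limits the point in four ways.

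- A reader might infer that the study is underpowered outright or needs some 77,500 births per period. The article does not support that. Its goal of 60 DOT per 1000 is well powered with all sites and, ignoring clustering, roughly so at an average site. Only the claim for a 10% reduction fails.
- A reader might take 49% as the power of the primary analysis. It is not: it belongs to a two-group test on means. The section gives no calculation for the mixed-effects model. The 2500 average is quoted for Dutch hospitals generally, not for these sites, and a rank test could do somewhat better if starts drive the change.
- A reader might conclude that site-level tests should be dropped. That does not follow, since an average site can detect a fall of about the size of the goal.
- A reader might trace the SD to the quoted range, since (491 − 54)/4 = 109.25. That gives about 1,377, close to 1395, but the article does not state its source. The error does not depend on it.

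Nor does the article say that a non-significant overall result will be read as no relevant reduction. It promises confidence intervals for level and trend changes, and it comments on null findings only for hospitals with already low DOT.

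None of this rescues the stated figure. An SD of 0.11 lies below the mathematical minimum for births, so no analysis plan could supply an SD that makes 1395 right.

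**Conclusion.** The statement that 1395 births per group give 90% power for a 10% reduction is wrong on the paragraph's own inputs. Power for that comparison is about 7% at 1395 births and 9% at an average site. With all sites it is about 49% if they average 2500 births, and 23–63% over the quoted birth range. These figures assume the stated treatment mix, a two-sided 5% test on means, SD 0.82 in both periods, no clustering and no secular trend. The single-site feasibility claim fails for a 10% reduction under any possible distribution of whole days, because even the minimum SD needs about 13,500 births per group against at most 3500 quoted for a hospital. The error should be corrected before results are interpreted. It does not undermine the design or the power for the stated goal.

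**What to change.** Revise the Sample size paragraph as follows.

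- Replace the figure of 2790 (1395 per group) and its 90% power claim with the per-birth SD of 0.82 day and its derivation.
- Give power for a 10% reduction as a range, using the actual births at the 11 sites and stating the assumptions: a two-group test on means, clustering ignored.
- Give the reduction detectable with 90% power: about 23 DOT per 1000 (17%) at 27,500 births per period, and about 19 to 36 per 1000 over the quoted birth range.
- For the goal of 60 DOT per 1000, state about 1,660 births per group (post-period SD 0.47) to 2,510 (SD 0.82 in both periods).
- State that these figures do not give the power of the mixed-effects time series model.
- Withdraw the claim of feasibility in most individual sites for a 10% reduction. Say that an average site can detect only about 75 DOT per 1000, so a null site-level result must not be read as showing no relevant difference.

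The cost is one reworded paragraph and a less favourable power statement. Design, data collection and planned tests stay as they are.

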However, all aforementioned interventions are not yet integrated into the Dutch national guideline on EOS management, which was most recently revised in 2017.^21^ Some Dutch hospitals already adopted one or more of the antibiotic stewardship interventions independently, but they are not applied in the vast majority. To integrate novel evidence into daily practice, active implementation should take place that carefully considers determinants influencing its application, including perspectives of all stakeholders.^22 23^ One of the challenges in the transition from evidence to practice is that most clinical interventions are researched primarily in controlled settings, yielding type 1 and 2 evidence on disease aetiology, burden and intervention effectiveness. As a result, there is limited type 3 evidence on how these interventions function in real-world environments, making it unclear what should be targeted for effective implementation.^24^ Moreover, since interventions are usually studied individually, little is known about how they interact with other evidence-based approaches for the same disease. Regarding neonatal antibiotic stewardship, several studies have reported the effect of implementing antibiotic stewardship interventions, yet reported mainly the impact on antibiotic prescription rates rather than data on the implementation context and strategies.^25 26^ The few studies that did emphasise implementation strategies were conducted at neonatal intensive care units with Level IV facilities.^27 28^ In contrast, most Dutch late preterm and term neonates at increased risk of EOS are born and treated in secondary hospitals (Level I–II facilities) and receive care in collaboration with the obstetric department and primary neonatal care.

Therefore, the primary aim of this study is to assess the impact of the strategy to implement an antibiotic stewardship bundle (the EOS calculator, PCT-guided therapy and IV-to-oral switch therapy) on antibiotic exposure for EOS in Dutch secondary hospitals. Secondary aims are to assess additional clinical outcomes and implementation outcomes, including the acceptability, feasibility and fidelity of the interventions, as well as the appropriateness of the implementation strategies.

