## Method

### Study design

This study is part of the Protect-Neo implementation project and focuses on the implementation and evaluation phase of the project. We will perform a multicentre, prospective, interrupted time series (ITS) and before-after implementation study. Mixed methods will be used to integrate clinical outcomes with implementation outcomes. The study runs from January 2024 to June 2026 and comprises a 9-month implementation period followed by a 12-month post implementation period during which data are collected. In addition, a 12-month pre-implementation period (January–December 2023) provides baseline data for the comparison of clinical outcomes (figure 1). The implementation period is divided into two distinct phases: a 6-month preparation phase (eg, change of local protocols, informing stakeholders, lobbying for equipment), followed by a 3-month active implementation phase (educational sessions, spread of informative materials, etc.).

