### Study setting and population

The study is conducted at the paediatric or specialised neonatal departments of 11 Dutch secondary hospitals and their surrounding primary neonatal care networks, consisting of obstetric practices and maternity care services. In the Netherlands, neonates at risk for EOS are initially managed either in obstetric wards (Level I) or neonatal wards (Levels II–IV), depending on their age and clinical condition. Most late-preterm and term neonates receive care in secondary hospitals (Level I–II facilities). Following discharge, continuity of care is provided by midwives, maternity nurses and general practitioners. Midwives hold medical responsibility for the mother and clinically well-appearing neonates during the first 10 days postpartum, with support from maternity nurses in the home setting. In cases where neonates continue oral antibiotic therapy at home, medical responsibility remains with the paediatrician, while supported by primary care.

Participating sites were purposively sampled covering various Dutch regions to create a proper reflection of region-bounded differences in organisation of care. The study population is twofold: (1) neonates born at 34 weeks of gestation or later with suspected EOS that will receive care associated with the interventions and (2) paediatricians, paediatric residents, nurse practitioners, neonatal nurses, maternity nurses and parents who are the focus of the implementation strategies. Other involved professionals are pharmacists, microbiologists, midwives, gynaecologists and gynaecologic residents.

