#### Secondary implementation outcomes—antibiotic stewardship interventions

We will determine the adoption of the three antibiotic stewardship interventions on department level. The fidelity to the antibiotic stewardship strategies will be determined on patient level, by calculating the proportion of eligible patients in which the intervention was applied. Professionals’ reported feasibility and acceptability of the interventions will be assessed to understand levels of adoption and fidelity and to inform possible future refinements of the interventions.

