#### Surveys

All paediatricians of the participating sites will be invited to complete a survey both before and 1 year after the active implementation period to assess changes in knowledge and practice gaps and the adoption of the interventions. Additionally, the post implementation survey will evaluate fidelity to and appropriateness of the implementation strategies 1–3 and 8 and assess acceptability and feasibility of the antibiotic stewardship interventions (onlinesupplemental files 4  5). Paediatric residents will only take part in the post implementation survey, as their frequent rotations across different workplaces make pre-implementation comparisons unfeasible. Neonatology nurses will also be invited to complete a survey, specifically to assess the acceptability and feasibility of IV-to-oral switch therapy and the fidelity to and appropriateness of strategies 1, 6 and 7 (online supplemental file 6). All surveys will be distributed via the Castor EDC system.

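### A null result in a low-DOT hospital is taken as proof of good practice, although a one-hospital comparison has only about 6–10% power for the plan's own 10% effect

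*Protocol article*

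**What the plan says.** The Sample size section first claims that the required 2790 births (1395 per group) can be reached in the whole study and at most individual sites, so a reading per hospital is contemplated. It then warns that "in hospitals with already low pre-implementation DOTs, no differences in absolute DOTS or trends may be found", and comments: "This is acceptable, as this would demonstrate that these hospitals are already leading in the reduction of antibiotic use". It adds that enlarging the sample to find a difference in such hospitals would serve no clinical purpose. It gives no cut-off for a low baseline, no precision requirement, and no link to what the hospital was actually doing.

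On prior use, the Introduction says of the country as a whole: "Some Dutch hospitals already adopted one or more of the antibiotic stewardship interventions independently, but they are not applied in the vast majority". Study setting and population describes selection by region: "Participating sites were purposively sampled covering various Dutch regions to create a proper reflection of region-bounded differences in organisation of care". It states no rule on prior use in either direction. Under Study design, "a 12-month pre-implementation period (January–December 2023) provides baseline data for the comparison of clinical outcomes".

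Implementation is measured. Paediatricians are surveyed "before and 1 year after the active implementation period to assess changes in knowledge and practice gaps and the adoption of the interventions", and fidelity is obtained "by calculating the proportion of eligible patients in which the intervention was applied". Neither measure is tied to the reading of a site-level null.

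**The concern.** The sentence turns absence of a detected difference into a positive finding. A low-baseline hospital that does not change could be already optimal. It could also have failed to implement the bundle, have had a chance-low 2023, or have improved by too little for its size to show. The result looks the same in all four cases, and the sentence names only the first.

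At stake is what is concluded about individual hospitals. With the sentence as printed, a low-baseline site where the strategy did not work would be reported as a leader, and its lesson for the process evaluation could be lost. Because a low baseline is judged on the same noisy year that serves as comparator, regression to the mean pushes such sites towards an apparent null even when they improve.

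**Working it through.** **Inputs (all from Sample size):** 3.8% of live births start antibiotics; 68.5% of these are treated for 2 days and 31.5% for 7 days; the relevant effect is a 10% reduction, to 121.5 per 1000; power 90%, alpha 5% (two-sided assumed, as sidedness is not stated); 1000 to 3500 births per hospital-year, about 2500 on average; quoted international range 54–491.

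**1. The plan's own figures.**
- Baseline: 0.685 × 38 × 2 + 0.315 × 38 × 7 = 135.85, matching the stated 136.
- The post-implementation value 121.5 equals 0.9 × 135, a difference of 13.5 per 1000.
- The sample size needs an SD, which is not stated. With n = 2(1.96 + 1.2816)² × SD² / 13.5², 1395 per group corresponds to an SD of about 110 per 1000. One quarter of the quoted range, (491 − 54)/4 = 109.25, gives 1377. That this was the source of the SD is only an inference.

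**2. Per-birth SD implied by the stated mix.**
- Mean = 0.038 × (0.685 × 2 + 0.315 × 7) = 0.13585 DOT.
- Mean square = 0.038 × (0.685 × 4 + 0.315 × 49) = 0.038 × 18.175 = 0.69065.
- SD = √(0.69065 − 0.13585²) = 0.820 DOT, or 820 per 1000.

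**3. Power of one hospital-year against another for 13.5 per 1000.** SE of the difference = 820 × √(2/n). Power is the chance of a significant fall, Φ(13.5/SE − 1.96).

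| Births per year | SE of difference | Power | Chance of no significant fall |
|---|---|---|---|
| 1000 | 36.7 | 5.6% | 94% |
| 2500 | 23.2 | 8.4% | 92% |
| 3500 | 19.6 | 10.2% | 90% |

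At 1395 births per group, power is 6.4%. Reaching 90% would take about 77,500 births per group.

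**4. How far a low baseline can be chance.** SE of one year's rate = 820/√n = 25.9, 16.4 and 13.9 per 1000 at 1000, 2500 and 3500 births. For a true rate of 136:
- 95% of single-year rates lie in about 85–187 (1000 births) or 104–168 (2500 births).
- The chance of a year at least 10% low is Φ(−13.6/SE): 30%, 20% and 16% respectively.
- Example: a hospital truly at 135.85 that records 10% too few has a baseline of 122.3. If it then truly falls by 10%, its expected later rate is also 122.3, so the expected observed change is zero.

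**5. A hospital that really is low.** Assume 54 per 1000 (bottom of the quoted range), the same 2-day/7-day mix and 2500 births. Power is 5.6% for a 10% cut and 45% for a 50% cut. The 95% CI half-width for the change is about 29 per 1000, more than half of the baseline itself.

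All these figures ignore clustering and overdispersion, which would lower power further.

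**The case against.** The strongest reply is that this is a sample-size remark, not a decision rule. It explains why the study is not enlarged for hospitals with little left to gain, and it sets no success criterion. The primary analysis is a pooled mixed-effects model with 95% CIs, between-hospital variability, random intercepts and random post-intervention slopes. Mixed methods will integrate clinical results with adoption and fidelity. This stands as far as the pooled result goes: nothing in the sentence excuses a pooled null. It does not rescue the sentence, which states what a site-level null shows, in a section that also calls the sample adequate for most single sites.

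Second, true differences between hospitals may be large. With an assumed between-hospital SD of 20, 40 or 110 per 1000 and the SE of 16.4, about 60%, 86% or 98% of the observed variance would be real (for example 20²/(20² + 16.4²) = 60%). A rate of 54 lies (136 − 54)/16.4 = 5 SEs below 136. So a very low baseline is unlikely to be chance alone; a moderately low one can be. Even a truly low rate does not show why it is low, and the null adds almost nothing to it.

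Third, single-site data are not useless. For the plan's ambitious goal (136 to 60), the same formula gives 54%, 91% and 97% power at 1000, 2500 and 3500 births. That applies to a hospital starting near 136, not to the low-baseline hospitals the sentence is about.

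A reader might also infer that the 2023 baseline is already partly exposed to the bundle. The documents do not support this. The Introduction speaks of Dutch hospitals in general and says that most do not apply the interventions. Nothing says that any participating site used an element in 2023, and detailed site criteria may stand in the full protocol.

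**Conclusion.** The point holds for the site-level inference. On the plan's stated mix, a single hospital's year-on-year comparison misses a real 10% reduction about 90–94% of the time, and a baseline at least 10% low arises by chance in about 16–30% of hospital-years. A null therefore demonstrates nothing about a hospital's standing. The calculation rests on independent births, the 2-day/7-day split, a two-sided 5% test and the quoted range of births per hospital.

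Two stronger readings should not be drawn. The sentence does not let the study as a whole excuse a failed implementation, because the primary inference is pooled. Exposure of the participating sites to the bundle before 2024 is possible but not established; if present, it would bias the pooled effect towards no change and could not create a false benefit.

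**What to change.** Replace the sentence in Sample size with a rule for reading single-site results:
- Report each hospital's change with its 95% CI. Call a null inconclusive unless the CI excludes a 10% reduction, whatever the baseline DOT.
- Describe a hospital as already leading only on direct evidence: documented use of the bundle elements in 2023 together with a low baseline DOT whose CI supports it. Never conclude this from the null. A written local protocol alone is not enough either, since it does not show fidelity.
- Record for each site which of the three elements were in the local protocol in 2023, and add one pre-specified sensitivity analysis of the pooled interrupted time series restricted to sites with no documented prior use.

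Interaction terms for three interventions on 11 hospitals and about eight quarters would be a debatable trade-off; the restricted analysis is simpler.

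**Cost.** A changed sentence, one site-level item and one extra analysis. The item may have to be asked of the sites: the logbook covers the implementation phase and its preparation, and the first survey need only precede active implementation, which follows a 6-month preparation phase in which local protocols change. The restricted estimate rests on fewer sites and has a wider interval. Most single-site nulls will be labelled inconclusive: at 136 per 1000 and 2500 births the CI half-width is 1.96 × 23.2 = 45.5, so excluding a 13.5 fall would need an observed rise of about 32 per 1000. That is an accurate account of what one site can show.
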